### Sample size

A review of the performance of saliva samples among adults and children by Laxton *et al*. reported concordance between saliva sampling and the reference comparator between 93 and 100%, depending on the studies and pathogens considered [12]. Accordingly, a 95% concordance is expected in our study. In the clinical context of bronchiolitis diagnosis, a 5% discordance (false-positive and false-negative results) is considered acceptable to validate the use of saliva samples instead of NPA. For a precision of 2% for the 95% confidence interval of the overall agreement (total interval length of 4%), it is necessary to analyze 457 patients. We estimate that a maximum of 10% of the children included will not be available for one of the two tests (insufficient sample volume, refusal of a second sample, etc.). It is therefore necessary to include 502 children.

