**Specifications table**

**Table utbl0001:** 

**Subject area**	Medicine and Dentistry
**More specific subject area**	Pediatric respiratory virology
**Name of your protocol**	Evaluation of the diagnostic capabilities of saliva samples from pediatric patients with respiratory symptoms, promoting the active involvement of the individuals concerned and their families: a randomized, intra-individual study.
**Reagents/tools**	Saliva collection tube: ORACOL+ (Malvern Medical, Worcester, UK) Mucus suction device (40mL), suction catheter appropriate for the child's age (ch6/8) qPCR reagents: Alinity m Resp-4-Plex Assay (Abbott Molecular Diagnostics, Abbott Park, Illinois, USA); AllPlex Respiratory Panels Assays 2, 3 and PneumoBacter (Seegene Inc, Seoul, South Korea)
**Experimental design**	Bronchiolitis is a common viral respiratory infection in children under 2 years of age and is responsible for a significant number of hospitalizations. This study aims to evaluate the reliability and comfort of a noninvasive saliva sample for detecting respiratory pathogens in infants with bronchiolitis. The project will be based on intra-individual randomization (crossover) of 502 children at the University Hospital of Poitiers. Each patient will undergo both sampling techniques; randomization will determine the order in which the samples are taken.
**Trial registration**	This study was registered in the Clinical Trial Registry (NCT07350291)
**Ethics**	This research will respect the principles and foundations of the Helsinki Declaration and Good Clinical Practice. It will also be registered with a personal data protection committee in accordance with current French legislation prior to any recruitment. The results of this study will be disseminated through presentations at scientific conferences and publication in peer-reviewed journals.

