### Data analysis

The type I risk will be 5% for all analyses. The 95% confidence intervals (CI) will be estimated by non-parametric bootstrapping (1,000 resampling), especially because of the low prevalences of pathogens and the related non-gaussian distributions. No interim analyses are planned. No correction of the multiplicity of tests will be performed. The analysis of the secondary endpoints will therefore be considered exploratory.

Because we expect a low percentage of missing values and missingness is at random, complete case analyses will be performed, i.e., patients with a missing value on the NPA-based test or the saliva-based test will not be considered in the analyses. The baseline characteristics (listed in the previous subsection) of the excluded patients will be compared with those of the analyzed population. If we observe differences, i.e., a non-random process, the outcomes’ analyses will be based on multiple imputation to reduce the risk of bias due to missingness (50 imputed databases, and confidence intervals obtained from the 5,000 resulting bootstrap samples).

*Descriptive analysis.* A description of demographic and clinical characteristics will be provided using means and standard deviations for continuous characteristics, or percentages and effectives for categorical characteristics. This description will be performed for the overall sample and according to the overall agreement (primary outcome) of the saliva-based and the the NPA-based tests.

*Analysis of the primary outcome.* We will estimate proportion of overall agreement and the related 95% CI. The agreement will be the diagnostic the same pathogens in-between the NPA-based and the saliva-based tests. More precisely, consider the following table for a pathogen where . The overall agreement is defined as

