### Limitations of the protocol

The primary outcome is the overall agreement between the two tests. The primary outcome will be affected by the microbial epidemiology of respiratory infections, which may vary each year. Even if some tendencies can be predicted in seasonality, the emergence of a new viral lineage or variant may occur [1,15]. The proportion of atypical bacteria, such as *Mycoplasma pneumoniae* and *Chlamydophila pneumoniae*, is also unpredictable, as they are known to cause epidemics every 5 to 7 years (16). This issue could be partially addressed by the 3-year study design, which will limit the impact of epidemiologic variations.

The required sample size was calculated according to this primary outcome, whose agreement can be inflated by many double-negative samples. The other results, i.e., discordant and double-positive samples, will be important to consider to better appraise the usefulness of saliva-based tests. Nevertheless, the related confidence intervals could be large.

The single-center study design may also affect the findings, as the standard of care and procedures may vary from those of other hospitals. This study should be considered a pilot study and, if the primary endpoint is achieved, will be followed by a randomized, multicenter national study for definitive validation of the use of saliva sampling in children with bronchiolitis or respiratory symptoms in pediatric departments.

Some patients may be excluded from the study if one of the two samples cannot be obtained or analyzed (e.g., if the volume is too low for analysis). A 10% loss of samples has already been considered when determining the sample size to address this issue. Moreover, the saliva sponge swab that will be used in this protocol has already been widely used in several studies and has proven successful in recovering enough saliva for further analyses.

Our study aims to evaluate the opportunity to replace NPA, the current reference approach in clinical practice, by saliva sampling. Importantly, NPA does not represent an absolute gold standard.

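### At the stated maximum loss of 10%, including 502 children leaves about 452 to analyse, not the required 457; the loss was added to the analysable number instead of divided out

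*Protocol article*

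**What the plan says.** The protocol article sizes the trial on the precision of the overall agreement between saliva and nasopharyngeal aspirate (NPA) results. The Sample size section sets out the chain as follows.

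- Expected agreement: "Accordingly, a 95% concordance is expected in our study".
- Target: a 95% confidence interval of ±2 points, 4 points in total length.
- Number to analyse: "it is necessary to analyze 457 patients".
- Loss: "We estimate that a maximum of 10% of the children included will not be available for one of the two tests".
- Conclusion: "It is therefore necessary to include 502 children".

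The article does not print the formula that leads from 457 to 502. The Experimental design row of the Specifications table gives the same total, "intra-individual randomization (crossover) of 502 children". The Limitations section does not repeat the total but relies on the allowance: "A 10% loss of samples has already been considered when determining the sample size". Under Data analysis, the default is a complete-case analysis that leaves out any child lacking either test result. Multiple imputation replaces it only if the excluded children are seen to differ from those analysed.

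**The concern.** The section fixes three things: the number needed for analysis, the loss rate, and the base of that rate, which is the children included. Together they determine the number to include, and it is not 502. The printed total fits a different calculation, in which 10% of the analysable number is added on top.

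What is at stake is the consistency of the trial's headline number with its own inputs. An allowance for a maximum loss should still hold when that maximum occurs, and this one falls slightly short. Because children with an incomplete pair leave the default analysis, the shortfall would reach the primary estimate, though only as a very small loss of precision.

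**Working it through.** **Inputs** (Sample size section unless noted)

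- Expected agreement p = 0.95
- Half-width d = 0.02
- Two-sided 95% confidence interval, z = 1.96 (Data analysis: "The type I risk will be 5% for all analyses")
- Number to analyse: 457
- Maximum loss: 0.10 of the children included
- Number to include: 502

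**Step 1. Reproduce the number to analyse.** The usual normal-approximation formula is n = z² × p(1 − p) / d².

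1.96² × 0.95 × 0.05 / 0.02² = 456.19, rounded up to 457. The plan's figure is confirmed.

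**Step 2. Find where 502 comes from.**

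| Calculation | Result |
|---|---|
| 457 × 1.10 | 502.7 |
| 456.19 × 1.10 (before rounding) | 501.8 |
| 457 / 0.90 | 507.8, so 508 |

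Only the multiplications by 1.10 lead to 502, either by truncating 502.7 or by rounding 501.8 up.

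**Step 3. Number needed under the stated base.** If a tenth of N included children is lost, 0.90 × N remain, so N must be at least 457/0.90 = 507.8.

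- N = 508: 508 × 0.90 = 457.2, which is enough.
- Difference from the plan: 508 − 502 = 6 children, or 6/502 = 1.2%.

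**Step 4. What 502 delivers.**

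- At 10% loss: 502 × 0.90 = 451.8, about 452 analysable children, which is 5 short of 457.
- Largest loss that still leaves 457: (502 − 457)/502 = 45/502 = 8.96%.

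**Step 5. Effect on precision.** Half-width = 1.96 × √(0.95 × 0.05 / n).

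| Children analysed | Half-width (points) | Total length (points) |
|---|---|---|
| 457 | 1.998 | 3.996 |
| 452 | 2.009 | 4.018 |

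**The case against.** The strongest reply is that the discrepancy makes no practical difference, and as to consequence that is right. The article states precision in whole points, and with 452 children the half-width is still 2.0 to one decimal. The design rests on precision with no power calculation, so five fewer children change no error rate.

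Other uncertainties are much larger. The cited review gives concordance from 93% to 100%. With 457 children the same formula gives ±2.34 points at 93% agreement (1.96 × √(0.93 × 0.07 / 457)) and ±1.56 at 97% (1.96 × √(0.97 × 0.03 / 457)). The reported interval will in any case come from bootstrapping, not from this formula.

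It is also fair to say that 10% is a ceiling and that the Data analysis section expects few missing values. The shortfall arises only if the loss falls between about 9% and 10%. If the switch to multiple imputation were triggered, incomplete pairs could re-enter the analysis. None of this makes 502 follow from the printed inputs, because a total meant to cover a stated maximum should cover it.

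A reader might infer more than the documents support:

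- **That the total was wrongly rounded down.** This is not established. The inflation formula is not given, and 501.8 rounded up also yields 502.
- **That the wrong total is repeated in the Limitations section.** It is not. That section mentions only the 10% allowance. The total reappears in the Specifications table.
- **That the trial is too small for its purpose.** A change of about 0.01 point in half-width does not support that.

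**Conclusion.** The point holds as a minor correction. The stated total was reached by adding the loss to the analysable number, whereas the stated base of the loss calls for division by 0.90. The gap is six inclusions, and the primary estimate is not threatened.

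The conclusion takes the loss at its stated maximum, reads it as the text defines it (a share of inclusions), and assumes the default complete-case analysis. The precision figures also assume 95% agreement and the normal approximation that reproduces the plan's 457. Below about 9% loss there is no shortfall at all.

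**What to change.** Restate the figure in the Sample size section in one of three ways.

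1. Keep 502 and say that it leaves 457 analysable children if the loss is at most about 9%. The 10% in the Limitations section should then be brought into line.
2. Keep 502 and the 10% loss, and say that at this loss about 452 children are analysed, with a half-width of about ±2.01 points. The Limitations section can stay as it is.
3. Correct the target to 508 and change the total in the Specifications table to match. The Limitations section needs no edit.

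The first two options cost a sentence and no extra children. The third costs six more inclusions. The article describes ethics submission and the start of the trial as still to come, so on its own account the wording can be settled before recruitment.

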### Data acquisition

Data acquisition will be carried out by investigators or clinical research assistants using electronic case report software. The following data will be collected: age (in months), sex, medical history requiring consultation or hospitalization, time since the onset of respiratory symptoms, Silverman score, fever, use of anticoagulants, time required for each respiratory sample (NPA and saliva), immediate complications of each respiratory sample, failure to retrieve one sample, number of caregivers required for each respiratory sample, help from parents required for one of the respiratory samples, procedural discrepancies, pathogens detected, cycle threshold value for each pathogen, satisfaction of caregivers and parents using a 0–10 visual scale, and pain assessed during each procedure using the EVENDOL scale.

### Data analysis

The type I risk will be 5% for all analyses. The 95% confidence intervals (CI) will be estimated by non-parametric bootstrapping (1,000 resampling), especially because of the low prevalences of pathogens and the related non-gaussian distributions. No interim analyses are planned. No correction of the multiplicity of tests will be performed. The analysis of the secondary endpoints will therefore be considered exploratory.

Because we expect a low percentage of missing values and missingness is at random, complete case analyses will be performed, i.e., patients with a missing value on the NPA-based test or the saliva-based test will not be considered in the analyses. The baseline characteristics (listed in the previous subsection) of the excluded patients will be compared with those of the analyzed population. If we observe differences, i.e., a non-random process, the outcomes’ analyses will be based on multiple imputation to reduce the risk of bias due to missingness (50 imputed databases, and confidence intervals obtained from the 5,000 resulting bootstrap samples).

*Descriptive analysis.* A description of demographic and clinical characteristics will be provided using means and standard deviations for continuous characteristics, or percentages and effectives for categorical characteristics. This description will be performed for the overall sample and according to the overall agreement (primary outcome) of the saliva-based and the the NPA-based tests.

*Analysis of the primary outcome.* We will estimate proportion of overall agreement and the related 95% CI. The agreement will be the diagnostic the same pathogens in-between the NPA-based and the saliva-based tests. More precisely, consider the following table for a pathogen where . The overall agreement is defined as

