**Table utbl0002:** 

Effective (proportion)		Saliva-based test		Total
		Positive result	Negative result	
NPA-based test	Positive result	()	()	()
	Negative result	()	()	()
	Total	()	()	()

*Analysis of the secondary outcomes (a).* For each pathogen, the following estimations and related 95%CI will also be estimated with the use of NPA-based results as gold standards [13]. The positive and negative percent agreement are respectively equaled to and . The Cohen’s kappa coefficient is, where . Additionally, by considering the NPA-based as the reference, sensitivity and specificity are .and, respectively. In addition, positive and negative predictive values are and, respectively.

*Secondary outcomes (b-d).* The pain level, the parental satisfaction, and the time spent by caregivers will be compared according to the sampling technique (NPA versus Saliva) in terms of means by paired two-sample t-tests. The interaction with the order (saliva/NPA or NPA/saliva) will also be explored by mixed linear models.

*Secondary outcomes (e-g).* The causes of complications, procedural discrepancies, and non-conclusive results will be described in terms of frequencies and percentages. In addition, to compare the two techniques, the following three proportions will be estimated and compared by using McNemar test: i) the proportion of sampling with at least one event among the following complications: bleeding, irritation, and exposure of healthcare workers to biological agents; ii) the proportion of sampling which has necessitated multiple healthcare workers, repeated procedure, or cessation of care by the legal representative; iii) the proportion of interventions with non-conclusive results: insufficient sample volume, refusal of sampling, or laboratory measurement errors. The interaction with the order (saliva/NPA or NPA/saliva) will also be explored by mixed logistic models.

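### Bootstrap confidence intervals are chosen because pathogens are rare, but for per-pathogen positive agreement and sensitivity sparse counts are where the bootstrap fails

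*Protocol article*

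**What the plan says.** The Data analysis section fixes one interval method for the whole study and gives a reason for it: "The 95% confidence intervals (CI) will be estimated by non-parametric bootstrapping (1,000 resampling), especially because of the low prevalences of pathogens". It adds that the resulting distributions are not Gaussian. The level is conventional: "The type I risk will be 5% for all analyses".

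The paragraph on secondary outcome (a) extends this to each target: "For each pathogen, the following estimations and related 95%CI will also be estimated". The measures are positive and negative percent agreement, Cohen's kappa, sensitivity, specificity and the two predictive values, with the nasopharyngeal aspirate as reference. No other interval is named for small tables or for results of 0% or 100%.

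Three further statements bear on the point. Secondary endpoints are declared exploratory. If missingness does not look random, intervals will come from bootstrap samples pooled over 50 imputed databases. The Limitations section says of the discordant and double-positive results: "Nevertheless, the related confidence intervals could be large".

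**The concern.** A non-parametric bootstrap redraws the children who were observed, so it cannot produce an outcome that the sample lacks. When no aspirate-positive child was missed by saliva, no resample contains a miss, and the interval for positive agreement has zero width however few children it rests on. Using more resamples, or switching between percentile and basic limits, does not help, because every resample in which the measure is defined has the same value.

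Low prevalence combined with high agreement produces this situation, and the protocol expects both: it cites low prevalence as its reason for the method, and on overall agreement it says "Accordingly, a 95% concordance is expected in our study". At stake are the error bars on per-pathogen performance for sparse targets. A pathogen seen in a handful of children could be reported with an interval that implies certainty.

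**Working it through.** **Inputs.** From the Sample size section: expected agreement 95%, half-width 2%, "it is necessary to analyze 457 patients". From Data analysis: 95% level and 1,000 resamples. The article gives RSV as 50–80% of bronchiolitis cases (Background) but no prevalence for the rarer targets and no per-pathogen sensitivity. Those used below are assumptions, shown as ranges.

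**1. The plan's own figure.** n = 1.96² × 0.95 × 0.05 / 0.02² = 456.2, rounded up to 457. It reproduces.

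**2. All m positives detected.** Every defined resample gives m/m, so the bootstrap interval is 100–100%. The Clopper-Pearson lower limit is 0.025^(1/m) and the Wilson lower limit is m/(m + 1.96²).

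| Detected | Bootstrap | Clopper-Pearson lower limit | Wilson lower limit |
|---|---|---|---|
| 3/3 | 100–100% | 29% | 44% |
| 5/5 | 100–100% | 48% | 57% |
| 10/10 | 100–100% | 69% | 72% |
| 23/23 | 100–100% | 85% | 86% |

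**3. Coverage for a fixed number of positives, assumed true positive agreement 90%.** Sum the Binomial(m, 0.9) probabilities of those x whose interval contains 0.9. The bootstrap limits are the 2.5% and 97.5% quantiles of Binomial(m, x/m)/m. The chance that all m are detected, which gives zero width, is 0.9^m.

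| Positives m | 0.9^m | Bootstrap coverage | Wilson coverage |
|---|---|---|---|
| 3 | 73% | 27% | 97% |
| 5 | 59% | 40% | 92% |
| 10 | 35% | 65% | 93% |
| 20 | 12% | 88% | 96% |

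Nearly all the lost coverage comes from the zero-width intervals.

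**4. Coverage by prevalence.** Patient-level simulation with 457 children, 1,000 resamples, 3,000 trials per scenario and true sensitivity 90%:

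| Assumed prevalence | Zero-width intervals | Bootstrap coverage |
|---|---|---|
| 0.5% | 79% | 21% |
| 1% | 64% | 36% |
| 2% | 41% | 59% |
| 3% | 25% | 75% |
| 5% | 11% | 88% |
| 10% | 1% | 92% |

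Wilson covers 95–96% in these rows. At 20–50% prevalence, with true sensitivity of 80–95%, the bootstrap covers 93–95%.

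**5. Undefined resamples.** With x positives among 457, a resample contains none with probability (1 − x/457)^457. That is 37%, 13%, 5% and 0.7% for x = 1, 2, 3 and 5, so this matters only at one to three positives.

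**6. Where the method works.** For patient-level overall agreement of 95% with n = 457, exact bootstrap coverage is 94.6%. At 434/457 the bootstrap gives 92.8–96.9% and Wilson 92.6–96.6%.

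**7. Negative agreement and specificity.** For 450/450 the bootstrap gives 100–100%, and the Wilson lower limit is 450/(450 + 3.84) = 99.2%. Bootstrap coverage is 58% if the true value is 99.8%, 89% at 99.5% and 93% at 99.0%, but the error in the limit is below one percentage point.

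**The case against.** The strongest reply is about consequence. The primary analysis is sound, the affected estimates are labelled exploratory, and the Limitations section calls the study a pilot to be followed by a multicentre trial. First-line use of saliva in the hospital is tied to the primary objective, and no decision rule uses a per-pathogen interval. The two-by-two layout shows counts, so a reader would see 5/5 beside its interval. This stands, and it sets the severity. The exploratory label deals with multiplicity, however, and does not repair an interval that covers 27–65% instead of 95%.

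Four stronger readings are tempting and are not supported:

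- **That the main result is compromised.** Coverage there is 94.6%.
- **That most of the panel is affected.** The article speaks of low prevalences in general but gives no figure for the rarer targets.
- **That the method contradicts the Limitations section.** That section says only that intervals might be wide. Some will be wide and some will collapse, so the tension is real but is not a contradiction.
- **That specificity would be badly misstated.** The error is below one percentage point at 450/450.

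Handling of resamples without positives could reasonably be left to an analysis plan. The choice of interval could not, since the article commits to it and gives a reason.

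**Conclusion.** The point holds in a limited form and should be fixed. The stated reason for the bootstrap runs the wrong way for per-pathogen positive agreement and sensitivity, and for predictive values that rest on few positives. The collapse at 100% is a mathematical property of the method and needs no assumption. The coverage figures assume a true positive agreement of 90%. At 95% the loss is greater (37% coverage at 2% prevalence, 69% at 5%), and at 80% it is smaller (83% and 94%). The damage lies at prevalences of roughly 5% or less, reaching 10% if sensitivity is very high. It is confined to exploratory secondary outcome (a). Overall agreement near 95% and common agents such as RSV are essentially unaffected.

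**What to change.** In Data analysis, restrict the bootstrap and name other intervals for outcome (a):

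- Use Wilson or Clopper-Pearson intervals for per-pathogen positive and negative agreement, sensitivity, specificity and predictive values, with numerator and denominator beside each. Where a pathogen has no aspirate-positive child, state that sensitivity cannot be estimated.
- Keep the patient-level bootstrap for overall agreement. It performs well there, and it would remain suitable if the agreement measure (whose formula is not legible in the text at hand) pooled pathogens within a child, where a simple Wilson interval would not.
- For kappa, report no bootstrap interval when the table is sparse or agreement is perfect. Under perfect agreement kappa is 1 in every defined resample, so the same collapse occurs. State in advance what counts as sparse.
- If multiple imputation is triggered, combine the per-pathogen proportions with a multiple-imputation version of the score interval, because the present plan builds those intervals from bootstrap samples.

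No extra children or data are needed. The cost is a few sentences, a little more analysis work and wider intervals for rare pathogens. It is best settled before enrolment.

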### Primary outcome measure

To assess substitutability, the primary outcome will be overall agreement, i.e., a patient with a saliva-based test that diagnoses the same pathogens as the NPA-based test. Samples will be analyzed using the Alinity m Resp-4-Plex Assay (Abbott Molecular Diagnostics, Abbott Park, Illinois, USA) and AllPlex Respiratory Panels Assays 2, 3, and PneumoBacter (Seegene Inc., Seoul, South Korea). These assays allow the detection of flu A and B; SARS-CoV-2; RSV (A and B without distinction); adenovirus; enterovirus; metapneumovirus; parainfluenza (1 to 4 with differentiation); bocavirus (1 to 4 without distinction); coronavirus 229E; coronavirus NL63; coronavirus OC43; rhinovirus; *Bordetella parapertussis; Bordetella pertussis; Chlamydophila pneumoniae*; and *Mycoplasma pneumoniae*. All these assays use an exogenous internal control to ensure proper extraction, amplification, and the absence of PCR inhibitors.

Both samples will be analyzed at the same time to compare the results on fresh samples. Quantitative PCR analysis will be fully automated on all assays. However, only the NPA result will be visible to clinicians to avoid interfering with the study. In case of invalid results, samples will be tested a second time, possibly diluted if PCR inhibitors are suspected. All dilutions of a sample will be noted in the final analysis to ensure an unbiased comparison. Assays used in this study have not been approved for the saliva matrix, but use the same extraction protocol that has been validated on SARS-CoV-2 assays [9,10]**.**

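### Primary agreement leaves out failed saliva samples, so taken alone it overstates how often saliva could replace NPA, and a baseline check decides whether missing results are imputed

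*Protocol article*

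**What the plan says.** All references are to the protocol article.

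- **Purpose** (Primary outcome measure): "To assess substitutability, the primary outcome will be overall agreement". Strengths of the protocol adds that success may lead the hospital to consider saliva as its first-line sample in children under 2.
- **Expected result and tolerance** (Sample size): "Accordingly, a 95% concordance is expected in our study", and "a 5% discordance (false-positive and false-negative results) is considered acceptable to validate the use of saliva samples instead of NPA".
- **Expected loss** (Sample size): at most 10% of children will lack one of the two tests, for reasons such as low volume or refusal of a second sample. The figure is not split between saliva and NPA.
- **Default rule** (Data analysis): "Because we expect a low percentage of missing values and missingness is at random, complete case analyses will be performed". A child lacking either result is left out. Limitations of the protocol confirms this: "Some patients may be excluded from the study if one of the two samples cannot be obtained or analyzed".
- **Switch** (Data analysis): excluded and analysed children are compared on baseline characteristics. A difference is read as a sign that the loss is not random, and the outcome analyses then "will be based on multiple imputation to reduce the risk of bias due to missingness". The article does not say what counts as a difference.
- **Where failures appear** (Secondary outcome measures, item g, and its analysis): low volume, refusal and laboratory error are described by technique, and the two techniques are compared with a McNemar test. Secondary endpoints are declared exploratory.

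**The concern.** There are two linked issues.

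**The denominator.** A child whose saliva cannot be obtained or read, but whose NPA is conclusive, is a child for whom saliva did not replace NPA. That child cannot lower the primary figure. Under the default rule the child is dropped. Under the fallback a result is filled in for a sample that gave none. The conclusion the trial wants to draw concerns replacing NPA in practice, and the primary number alone does not answer that.

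**The switch.** Which of two methods yields the primary estimate depends on a comparison made on the trial's own data. The reasoning attached to it is also loose. Complete-case estimation of a simple proportion generally needs more than missingness at random. A baseline difference is no evidence of a non-random mechanism, and the absence of one does not show the loss to be harmless.

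At stake is whether a reader takes 95% agreement to mean that saliva would have served in 95% of eligible children.

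**Working it through.** **1. The plan's own figure.** Inputs from Sample size: agreement p = 0.95, half-width d = 0.02, two-sided 95% interval.

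n = z² p(1 − p) / d² = 1.96² × 0.95 × 0.05 / 0.02² = 456.2, rounded up to 457. This matches "it is necessary to analyze 457 patients".

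For inclusion, 456.2 × 1.10 = 501.8, which gives the stated 502. Dividing by 0.90 would give 457 / 0.90 = 507.8, or 508. The gap is immaterial: 502 × 0.90 is about 452 pairs, with a half-width of 1.96 × √(0.95 × 0.05 / 452) = 2.01 points. The 10% allowance therefore protects precision. It does not change which children are in the denominator.

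**2. Counting saliva failures as non-agreement.** Let f be the saliva failure rate among children with a conclusive NPA. Then

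agreement with failures counted = agreement in valid pairs × (1 − f).

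Assumptions: NPA is conclusive in all 502 children, valid-pair agreement is the plan's 95%, and f is varied because the article gives no rate for saliva alone. Intervals are Wald.

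| Assumed f | Failed | Valid pairs | Agreeing (0.95 × pairs) | Agreeing / 502 (95% CI) |
|---|---|---|---|---|
| 0% | 0 | 502 | 476.9 | 95.0% (93.1 to 96.9) |
| 2% | 10 | 492 | 467.4 | 93.1% (90.9 to 95.3) |
| 5% | 25 | 477 | 453.15 | 90.3% (87.7 to 92.9) |
| 10% | 50 | 452 | 429.4 | 85.5% (82.5 to 88.6) |

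The valid-pair figure stays at 95.0% (about 93 to 97) in every row. A 2% failure rate lowers the other figure by 1.9 points, about the planned half-width.

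**3. Losses shared between the tests.** Take the plan's gap of 502 − 457 = 45 lost pairs, with 0.95 × 457 = 434.15 agreeing. Children without a conclusive NPA stay out of the denominator.

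- All 45 are NPA failures: 434.15 / 457 = 95.0%.
- Half are saliva failures: 434.15 / (457 + 22.5) = 90.5%.
- All are saliva failures: 434.15 / 502 = 86.5%.

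**4. What imputation estimates.** It estimates what the lost pairs would have shown had the samples worked, so it still counts no failure. Suppose the 45 lost pairs would have agreed only 80%, 70% or 50% of the time. Then (434.15 + 0.80 × 45) / 502 = 93.7%, and likewise 92.8% and 91.0%. If nothing observed predicts the loss, complete-case analysis and imputation assuming missing at random would both return about 95%.

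**5. The switch.** Baseline differences between excluded and analysed children argue against data missing completely at random. They are compatible with missing at random given those characteristics, which is where imputation works. So the action taken is reasonable and the label is wrong. With no difference, loss driven by the sample itself (scant volume, inhibitors) remains possible. Also, the subsection cited for the baseline list (Data acquisition) contains items recorded after sampling, such as failure to retrieve a sample, on which excluded children differ by construction.

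*Illustration only.* If the comparison were a set of separate two-sided 5% tests, which the article does not state, 50 excluded against 452 analysed gives 27% power for a 0.2 SD difference and 52% for 0.3 SD. With 45 against 457 the powers are 25% and 48%. Over seven independent pre-sampling items, the chance of at least one false alarm is 1 − 0.95⁷ = 30%.

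**The case against.** **Failures are not hidden.** Outcome g records them by technique and compares the techniques. Valid-pair agreement with failure rates beside it is an accepted two-number presentation. This stands, and a reader who inferred that the plan ignores failed samples would be wrong. What remains is that outcome g is exploratory and nothing ties it to the substitutability conclusion. Read literally, the exclusion rule would also strip the failures out of outcome g. That cannot be intended, since outcome g consists of them.

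**The 5% tolerance does not cover failures.** A reader might set 85.5% against the plan's 5% and conclude that saliva would miss its own benchmark. The documents do not support this: the tolerance is confined to false-positive and false-negative results, and a failed sample is neither.

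**The large figures are extremes.** The 10% is a maximum and covers both tests. NPA is the second sample in half the children and has its own minimum volume. Invalid results are retested, and the article reports good recovery with this sponge. Some saliva refusals would arise only because a second sample was asked for. All of this stands, so 85.5% is not a forecast.

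**The switch is coherent if at random is read loosely as completely at random.** This largely stands. It would be too strong to say that the switch tests the wrong thing or biases the estimate: under completely random loss, a false alarm leads to an imputed analysis that is also about unbiased. A criterion for a difference may sit in an analysis plan not shown, so its absence from the article is not the fault. The data-dependent choice of primary method is in the article itself.

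**The claim is modest.** The article speaks of a pilot and of possible first-line use, not of success in every child. That lowers the stakes but leaves the gap between figure and conclusion.

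**Conclusion.** The point holds in limited form. The primary figure estimates agreement among children in whom both samples worked. That is a legitimate quantity, but taken alone it overstates how often saliva could replace NPA once any saliva sample fails beside a conclusive NPA. Imputation does not remedy this.

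The direction is certain and the size is unknown. Assumed saliva failure rates of 2%, 5% and 10% move 95% to 93.1%, 90.3% and 85.5%, given 95% valid-pair agreement and a conclusive NPA in all 502 children. If the losses are all NPA failures, there is no overstatement.

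The switch makes the primary method data-dependent, mislabels covariate-related missingness as non-random, and cannot detect loss that depends on the sample. No resulting bias in the primary estimate has been shown, and the power and false-alarm figures rest on a testing rule the article does not state.

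**What to change.** 1. Keep agreement among valid pairs as the primary outcome and name it so.
2. Pre-specify beside it agreement among all children with a conclusive NPA, counting a saliva failure as non-agreement. Showing those failures by cause and sampling order would separate refusals that arise only because two samples were asked for.
3. Base the substitutability statement on both figures together with outcome g, and state that the exclusion rule does not apply to outcome g, which keeps the failed samples.
4. Replace the baseline-triggered switch with a multiple-imputation sensitivity analysis that is always run and is labelled as assuming missing at random. The baseline comparison can stay as description, limited to items recorded before sampling.

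The cost is some wording and one more proportion from data already collected. Sample size and procedures do not change. The downside is that a second, lower agreement figure is published.
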